### Ethics

Ethical approval for this study has been obtained from Southmead Research Ethics Committee, reference 08/H0102/95.

### Trial registration

Current Controlled Trials ISRCTN55666618

### Analysis

The main hypotheses are that PhysioDirect will be clinically equivalent to usual care and more cost-effective at 6 months after randomisation.

Analysis and presentation of data will be in accordance with CONSORT guidelines. The *primary analysis *will employ multivariable regression to investigate between-group differences in mean SF-36 PCS score at six months follow up. The primary analysis will be conducted on an intention-to-treat (ITT) basis, with due emphasis placed on the confidence interval for the between-arm comparison when inferring equivalence (or otherwise) of the two groups. Clinical equivalence between the arms will only be concluded if the 95% confidence interval for the primary outcome lies wholly inside the range -0.2 to 0.2 SDs. Given the equivalence design and the generally conservative nature of ITT analysis, between-group differences will also be investigated using methods that model compliance with the allocated treatment arm, such as instrumental variable regression. Analyses will adjust for minimisation variables and baseline outcome variable scores, and will take appropriate account of the hierarchical nature of the data (practice and physiotherapy site).

In the *economic analysis *mean cost to the NHS per patient in each arm will be compared with mean gain in quality adjusted life year (QALY) using the EQ5D in order to estimate a cost-utility ratio of incremental cost per QALY gain. Secondary analysis will explore the QALY gain using the SF-6D [34], derived from the SF-36. A cost-consequences matrix will be used to present a comparison of cost per patient in each group from the patient and societal perspectives with a range of outcomes, for example, personal perception of improvement and patient satisfaction. The effect of uncertainty in unit cost estimates or assumptions about resource use will be addressed in sensitivity analyses. Using a bootstrapping approach for data analysis, the results of the economic analysis will be presented using cost-effectiveness acceptability curves.

### Secondary analyses

are summarised in Table 2.

**Table 2 T2:** Secondary analyses:

(1)	Assessing equivalence in clinical outcome using the MYMOP2 score.
(2)	Examining clinical outcome at 6 weeks using the SF-36 PCS

(3)	Comparing the proportion of patients who 'respond to treatment' in each arm, in line with the Outcomes Measures in Rheumatology Clinical Trials- Osteoarthritis Research Society International (OMERACT-OARSI) recommendations [30], using the SF-36 physical function and bodily pain scales and the global improvement score

(4)	Repeating the primary analysis adjusting also for any variables exhibiting marked imbalance at baseline to check that this does not influence the findings

(5)	Analyses as above for secondary outcomes (where p-values will be adjusted to account for multiple testing)

(6)	Investigating the effectiveness and cost-effectiveness of PhysioDirect for patients of different age-groups, or with different presenting problems

(7)	Investigating the effectiveness and cost-effectiveness of PhysioDirect in each of the four PCTs, in exploratory sub-group analyses

(8)	Investigation of process measures such as physiotherapy consultation rates, physiotherapy 'did-not-attend' rates and consultation rates with other health care services in the NHS and private sectors

#### Sub-group analyses

Appropriate interaction terms will be entered into the primary regression analysis for SF-36 in order to conduct pre-specified subgroup analyses according to presenting complaint, patient age-group, socio-economic status and PCT. Since the trial is powered to detect overall equivalence between the groups rather than interactions of this kind, the results of these essentially exploratory analyses will be presented using descriptive statistics and, where helpful, confidence intervals as well as p-values, and interpreted with due caution.

Although the study is powered in relation to patient level outcomes, some of the outcomes will be strongly clustered by physiotherapy site (particularly waiting times). The analysis of these outcomes will be descriptive only.

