### Participants

The inclusion criteria are as broad as possible in order to maximise generalisability and to reflect the 'real-world' operation of PhysioDirect services. Inclusion criteria are adults (aged 18 years or over) who are referred by GPs or other members of the primary health care team, or who refer themselves (self-referred) for musculoskeletal physiotherapy.

Exclusion criteria are children (< 18 years); patients referred to physiotherapy by a hospital consultant, emergency department or primary/secondary care interface service; those needing domiciliary physiotherapy; those needing post-operative physiotherapy; those needing physiotherapy for non-musculoskeletal problems; those unable to communicate by telephone in English.

GPs or health care professionals in the relevant practices will refer patients to physiotherapy in their usual way, or patients may refer themselves. Referral forms will be screened by a senior physiotherapist within one working day to confirm that the patient is potentially eligible, and eligible patients will be sent information about the trial by post, along with a consent form and a baseline questionnaire. Patients who give consent to participate and complete the baseline questionnaires will be randomised in a 2:1 ratio to PhysioDirect or usual care. This allocation ratio was chosen to ensure that sufficient people are randomised to PhysioDirect to make it viable to establish this new service, given that non-consenting and excluded patients will continue to receive usual care as well as those randomised to usual care. Randomisation will be undertaken using web or telephone access to a secure remote allocation system, with allocation made at the level of the individual, minimising by PCT, gender, patient age group and presenting complaint. Following randomisation, patients will be sent a letter either inviting them to contact PhysioDirect and telling them how to do so (intervention arm), or telling them that they are on a waiting list for a face-to-face appointment (control arm).

The number of patients excluded from the trial for different reasons will be recorded. The age and sex of all patients will be recorded in anonymised form, to make it possible to compare participating and non-participating populations. Eligible patients who decline to participate will receive usual care.

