### Collection of data

The baseline questionnaire will collect data about patient characteristics and about the outcome measures. Data about outcomes at follow-up will be collected from postal questionnaires sent at 6 weeks and 6 months after randomisation. Data will be collected by telephone instead of post where patients do not respond to a postal questionnaire or a postal reminder, where patients express a preference for telephone administration, or where patients are unable to complete written questionnaires in English. Data about use of healthcare resources will be extracted from physiotherapy service records and medical records, and details of use of other resources will come from the patient questionnaires.

Table 1 lists the various outcome measures, the timing of data collection and the source of the data.

**Table 1 T1:** Outcome measures, timing of data collection and source of data

	**Timing**	**Source**
Patient identifiers, type of problem, age and sex	Pre-consent	Referral letter. Recorded (anonymised) in research database

Demographic details	Baseline	Baseline patient questionnaire

SF36v2	Baseline, 6 weeks, 6 months	Patient questionnaires

MYMOP	Baseline, 6 weeks, 6 months	Patient questionnaires

EQ5D	Baseline, 6 weeks, 6 months	Patient questionnaires

Overall perception of improvement	6 weeks, 6 months	Patient questionnaires

Time lost from work and usual activities	Baseline, 6 weeks, 6 months	Patient questionnaires

Satisfaction with care provided	6 weeks, 6 months	Patient questionnaire

Preference for Physiodirect or usual care	Baseline, 6 months	Patient questionnaires

Waiting time for treatment	Collected at end of study	Physiotherapy service records, from date of referral received to date first phone or face-to-face consultation

Patient and companion costs	6 weeks, 6 months	Patient questionnaires

Cost of lost production associated with time off work and usual activities.	6 weeks, 6 months	Estimated from information in patient questionnaires

Costs of providing physiotherapy	Set up costs: collected during set up phase and once the service is operating. Treatment over 6 months: collected at end of study.	Set up: data from PCTs about resources involved in setting up the service; Treatment: physiotherapy records, data collected within the trial about lengths of consultations, staff use of time, staff grades etc.

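### The age interaction is specified by age group although each patient's age is recorded; a continuous-age term should be added, because grouping loses information if the effect changes gradually with age.

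*Protocol article*

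**What the plan says.** Sub-group analyses states: "Appropriate interaction terms will be entered into the primary regression analysis for SF-36". The subgroups are fixed in advance, "according to presenting complaint, patient age-group, socio-economic status and PCT". The section then declares these analyses exploratory: "Since the trial is powered to detect overall equivalence between the groups rather than interactions of this kind".

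Table 2 item 6 uses the same unit: "Investigating the effectiveness and cost-effectiveness of PhysioDirect for patients of different age-groups, or with different presenting problems". The fourth research question is also worded by age group, alongside type of problem. Randomisation uses it too, "minimising by PCT, gender, patient age group and presenting complaint".

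Age itself is held at patient level. Participants says "The age and sex of all patients will be recorded in anonymised form", and the first row of Table 1 lists "Patient identifiers, type of problem, age and sex".

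The article does not give the number of age groups, the cut-points or the form of the interaction test, and it mentions no interaction with age as a continuous variable.

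**The concern.** Eligibility starts at 18 years with no upper limit, so an age band may span decades. A grouped interaction treats everyone in a band as the same age. With three or more unordered groups it also spreads a gradual change in effect over two or more degrees of freedom.

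Whether PhysioDirect does better or worse at some ages belongs to a stated research question, and the plan itself says the trial is not powered for interactions. Avoidable loss of information matters more in that setting: an imprecise interaction is easily read as evidence that age makes no difference. The better variable is already in the data.

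**Working it through.** **Plan's own figure.** The article states no figure for the age interaction, so there is none to reproduce.

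**Inputs from the article.** Age recorded per patient; interaction by age group; lower age limit 18; 488 usual care and 976 PhysioDirect patients analysed (Sample size and power calculations).

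**Assumptions, not in the article.** The effect changes linearly with age. Age is normal or uniform on 18-80; truncated normals from 18 to 95 (mean 48, SD 16; mean 50, SD 18) were also tried and fall between these two for equal-sized groups. Two-sided alpha is 0.05.

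**Benchmark.** A linear arm-by-age term that has 80% power. With 1464 analysed in a 2:1 ratio, this is a slope of (1.960 + 0.842) / √(1464 × 2/9) = 0.155 SD of outcome per SD of age, for a unit residual SD. The 80% is a reference point; the trial does not claim it for this test.

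**Step 1: joint test of k unordered groups.** Let S be the share of the variance of age that lies between groups. Let λ(df) be the non-centrality needed for 80% power: λ(1) = 7.85, λ(2) = 9.63, λ(3) = 10.90, λ(4) = 11.94. Then

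loss = 1 − S × λ(1)/λ(k−1).

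| Equal-sized groups | S, normal to uniform | λ(1)/λ(k−1) | Loss, uniform to normal |
|---|---|---|---|
| 2 (median split) | 0.636 to 0.750 | 1 | 25% to 36% |
| 3 | 0.792 to 0.889 | 0.815 | 28% to 35% |
| 4 | 0.860 to 0.937 | 0.720 | 32% to 38% |
| 5 | 0.896 to 0.960 | 0.658 | 37% to 41% |

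For example, three groups with normal age: 1 − 0.792 × 0.815 = 0.35.

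**Step 2: one-degree-of-freedom trend score over ordered groups.** Here loss = 1 − r², with r the correlation between age and the group score.

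| Ordered groups | Loss, uniform to normal |
|---|---|
| 3 | 11% to 21% |
| 4 | 6% to 15% |
| 5 | 4% to 11% |

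**Step 3: an uneven split.** A single cut at 65 keeps 0.45 to 0.55 of the variance of age (uniform and the two truncated normals), a loss of 45% to 55%.

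**Step 4: what a loss L means for power.** Power = Φ(√(1−L) × 2.802 − 1.960).
- L = 0.25: Φ(2.426 − 1.960) = Φ(0.466) = 68%.
- L = 0.40: Φ(2.170 − 1.960) = Φ(0.210) = 58%.

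**Step 5: the reverse case.** If the effect is really a step at the median age, the two-group test is the right one. The linear term then keeps only the squared correlation between age and the split indicator, 0.75 (uniform) or 0.64 (normal), and so loses the same 25% to 36%.

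**The case against.** The strongest reply has four parts.

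1. **The size of the loss is not in the document.** A reader might infer that the plan discards a quarter to 40% of the information as a matter of fact. The article does not support that: over reasonable choices of groups and test, the loss runs from about 4% to about 55%. This stands, so the figures can only be conditional.
2. **A linear benchmark favours a linear term.** A reader might infer that grouping brings no gain. Step 5 shows otherwise for a step-shaped effect, and the article gives no reason to prefer one shape. This stands too. It is why a continuous term should be added beside the groups, not put in place of them.
3. **The research question is itself worded by group.** A reader might infer that the fourth research question as a whole is damaged. It is not. Group estimates answer its wording directly, and it also covers type of problem and patients' experiences, which this point does not touch. Only its age component is concerned.
4. **The coding of interaction terms is commonly left to the SAP.** The article does leave the form of the terms open, and an SAP that is not shown could add age in years. This stands in part. The same sentence names age group as the pre-specified variable, so the coarser choice is stated and is not merely a detail left out.

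The analysis is also declared exploratory, no decision rule hangs on the interaction p-value, and the use of age groups is consistent across the article. That limits the consequence but does not remove the case for a one-sentence improvement.

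**Conclusion.** The point holds as a minor improvement. The plan names age group as the effect modifier while age is available for each patient. If the treatment effect changes gradually with age, this loses about 25-40% of the information relative to a linear arm-by-age term under a median split or a joint test of three to five unordered, equal-sized groups. It loses about 4-21% under a trend score over three to five ordered groups. Both ranges depend on the assumed linear trend and age distributions.

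Nothing here contradicts another part of the plan. The primary equivalence conclusion on the SF-36 PCS is unaffected.

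**What to change.** In Sub-group analyses, add one sentence: the arm-by-age interaction will also be fitted with age in years as a continuous variable (linear, with a check for curvature) and reported with its 95% CI. Keep the age-group estimates for display, and keep age group as the minimisation covariate in the model.

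The cost is a wording change and one further exploratory model, with no new data and no change to the design. The downside is weaker detection of a step-like effect by the linear term, so the text should say that the curvature check and the group estimates are to be read alongside it.

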#### Qualitative analysis

Analysis of the qualitative data will use an inductive, thematic approach based on the method of constant comparison. Data collection and analysis will be carried out iteratively so that emerging themes in the analysis can be explored in depth in further interviews. Sampling will continue until no new themes emerge. A researcher will code the transcribed data, with a sample of interviews being independently coded by a second researcher to ensure transparency and agree emergent themes at successive stages of the data collection and analysis. Negative or deviant cases will be investigated closely.

### Sample size and power calculations

This study is powered to establish clinical equivalence using the PCS scale from the SF-36. The minimum clinically important difference in a range of populations and conditions has been estimated as being at least 4 points (0.4 SD) [35-38]. However in this study a difference of no greater than 2 points has been specified as demonstrating equivalence. This is equivalent to an effect size of 0.2, which is considered a small effect size [38]. Sample sizes for analysis of 488 and 976 in the Usual Care and PhysioDirect groups respectively will yield 80–95% power to reject a null hypothesis of non-equivalence with an overall alpha of 0.05 alpha assuming that the observed difference in means is in the range zero to 0.045 SDs. The target sample size for patients completing the final six-month follow-up questionnaire is 1000 patients in the PhysioDirect arm and 500 patients in the Usual Care arm.

Assuming 20% non-collection of the primary outcomes, it will be necessary to recruit 1250 and 625 patients in the PhysioDirect and usual care arms respectively, or 1875 patients in total.

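### The stated 80–95% power is that of clearing one equivalence bound; the planned two-bound 95% CI rule has about 79–90%, at a type I error of 0.025 and not 0.05

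*Protocol article*

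**What the plan says.** The Analysis section of the protocol article sets one decision rule for the primary outcome, SF-36v2 PCS at 6 months. Equivalence will "only be concluded if the 95% confidence interval for the primary outcome lies wholly inside the range -0.2 to 0.2 SDs". Both limits must therefore clear their margins.

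The section on sample size and power sets the margin at 2 PCS points: "in this study a difference of no greater than 2 points has been specified as demonstrating equivalence". It equates this with 0.2 SD: "This is equivalent to an effect size of 0.2, which is considered a small effect size". The power claim, made for 488 usual care and 976 PhysioDirect patients analysed, is that these numbers "will yield 80–95% power to reject a null hypothesis of non-equivalence with an overall alpha of 0.05 alpha assuming that the observed difference"; the values considered for that difference run from zero to 0.045 SD. The same section sets a completer target of 500 and 1000 and, allowing 20% loss, a recruitment target of 625 and 1250. It mentions no allowance for baseline correlation or for clustering.

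**The concern.** A rule that needs the whole 95% interval inside two margins is two one-sided tests at 2.5% each, and the result is a success only if both reject. When the true difference is zero, the two bounds contribute equally to the chance of failure. A calculation that looks at one bound therefore gives about half the true failure probability. The gap shrinks as the true difference moves towards one margin, because the far bound then almost never fails.

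The stated alpha raises a second question. Two one-sided tests with a type I error of 0.05 correspond to a 90% interval, whereas the Analysis section specifies a 95% interval. Finally, the power is made conditional on the *observed* difference. Power is a property of the true difference; once the observed difference is fixed, little is left to chance.

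This is the only power statement for the primary hypothesis. If it belongs to a different test from the one the trial will apply, readers are given the wrong chance of an inconclusive result. They are also left unsure which error rate, and so which confidence level, governs the conclusion.

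**Working it through.** **Inputs (all from the protocol article).** Analysed: 488 usual care, 976 PhysioDirect. Margin m = 0.2 SD. Difference d = 0 to 0.045 SD. Rule: 95% interval inside both margins (Analysis section). Stated alpha 0.05 and stated power 80–95% (sample size section). Unadjusted comparison, since no correlation or design effect is given.

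**Standard error.** SE = √(1/488 + 1/976) = 0.05544 SD.

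**Formulas.**
- One bound: Φ((m − d)/SE − z)
- Both bounds: Φ((m − d)/SE − z) + Φ((m + d)/SE − z) − 1

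Here z = 1.96 for a 95% interval and 1.645 for a 90% interval.

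**Reproducing the printed figures: one bound, z = 1.96.**
- d = 0: 0.2/0.05544 − 1.96 = 1.647; Φ = 0.950
- d = 0.045: 0.155/0.05544 − 1.96 = 0.836; Φ = 0.798

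These are the stated 95% and 80%. The corresponding one-bound sample size formula with 95% power at d = 0 and 2:1 allocation, 1.5 × ((1.96 + 1.645)/0.2)², rounds up to 488 in the smaller arm.

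**The rule in the Analysis section: both bounds, z = 1.96.**
- d = 0: 2 × 0.9503 − 1 = 0.9005
- d = 0.045: the far bound is 0.245/0.05544 − 1.96 = 2.459, Φ = 0.993; so 0.798 + 0.993 − 1 = 0.791

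A simulation with t-based intervals gives the same: 90.0% and 79.1%.

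**All readings side by side (488 and 976).**

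| Test | d = 0 | d = 0.045 SD |
|---|---|---|
| One bound, one-sided 2.5% | 95.0% | 79.8% |
| Both bounds, 95% interval (the stated rule) | 90.0% | 79.1% |
| Both bounds, 90% interval | 95.0% | 87.2% |
| Both bounds, one-sided 1.25% each | 82.8% | 69.6% |

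No two-bound reading gives both 95% and 80%.

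**Completer target (500 and 1000).** SE = 0.05477 SD. Both bounds with a 95% interval: 90.9% at zero and 80.2% at 0.045 SD.

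**Type I error.** With the true difference placed at a margin, the two-bound 95% rule declares equivalence with probability 0.025. The 90% version gives 0.05.

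**What 95% at zero would take under the stated rule.** 1.5 × ((1.96 + 1.96)/0.2)² rounds up to 577, with 2 × 577 = 1154 in the other arm. After 20% loss: 577/0.8 → 722 and 1154/0.8 → 1443 recruited.

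**The case against.** Several points can fairly be made for the protocol.

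**The lower figure is sound in practice.** 79.1% against 80% is under one point, and the 500 and 1000 target gives 80.2%. The trial keeps its 80% floor. This stands, and it confines the material error to the upper figure.

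**The alpha may be only loosely labelled.** An overall 0.05 can be read as the two-sided level that goes with a 95% interval, 0.025 at each bound. The printed power pair does use z = 1.96, which supports this reading. On it, the two sections use the same critical value, and the slip is that power was computed for one bound. The label also hides no excess false-positive risk, because 0.025 is below 0.05. All of this is reasonable. Even so, 0.05 is not the probability of wrongly rejecting non-equivalence, which is how the sentence presents it.

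**The planned analysis adjusts for baseline.** The Analysis section requires this, and it could recover the power. The documents give no correlation, so a range must be assumed. Multiplying the SD by √(1 − r²) for 488 and 976 gives:
- r = 0.2: 91% at zero and 81% at 0.045 SD
- r = 0.3: 93% and 83%
- r = 0.4: 95% and 86%
- r = 0.5: 97% and 90%

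A correlation near 0.4 would restore 95% at zero, but the range would then be 86–95%, so this is not where the printed 80–95% comes from. The same section also plans to account for practice and physiotherapy site. If that inflates the variance by an assumed 1.05 to 1.1, power at zero becomes 88% to 86%, and at 0.045 SD 77% to 75%. The net effect of the two is unknown.

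**Observed for true is a wording slip.** Agreed; it changes no number.

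**Conclusion.** The concern holds. The printed 80–95% is the power to clear a single bound at one-sided 2.5%; the article does not say how the figure was obtained, but no two-bound calculation on its inputs returns it. Under the rule the trial will apply, 488 and 976 analysed give 90.0% at a true difference of zero and 79.1% at 0.045 SD. At the target of 500 and 1000 the figures are 90.9% and 80.2%.

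The weight lies in the upper figure, overstated by 4 to 5 points: with identical arms and 488 and 976 analysed, the chance of failing to conclude equivalence is about 10%, twice the implied 5%. The type I error of the rule is 0.025 at either margin, however the 0.05 was meant.

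These figures assume an unadjusted comparison of two means with a common SD and no clustering, which are the only inputs the article gives. The error does not leave the trial underpowered at the 80% level, and it does not affect the margin, the decision rule or recruitment.

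**What to change.** Keep the sample size, the margin and the 95% interval rule. Replace the power sentence in the sample size section with wording to this effect:

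*With 488 usual care and 976 PhysioDirect patients analysed, the probability that the 95% confidence interval falls entirely within ±0.2 SD is 90% if the true difference is zero and 79% if it is 0.045 SD (91% and 80% with 500 and 1000). Each bound is tested at one-sided 2.5%.*

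This removes the overall alpha of 0.05 and the reference to an observed difference, and it ties the power to the rule in the Analysis section. If the team wishes to claim the benefit of baseline adjustment, it should state the correlation assumed and any design effect alongside it.

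The cost is a change of wording and a slightly less favourable headline figure. No additional patients are required.
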